## Discussion

### PREPARE programming strategies

#### 1) Strategies to reduce shocks for VT/VF

##### ○ longer detection duration

VF initial beats to detect is set to 30 of 40 beats. At least 25% of ICD-detected VF is non-sustained VT/VF[15-17] The extended detection duration may decrease unnecessary shocks by allowing for spontaneous termination of non-sustained VT/VF that would otherwise be treated with nominal settings of shorter detection duration.

##### ○ ATP for FVTs 330–240 ms

One sequence of ATP will be delivered for FVTs using the FVT via VF zone. Approximately 81% of ICD-detected VF (<320 ms) is monomorphic VT. Monomorphic VT can be pace terminated 75% of the time with one sequence of ATP. [12,15,18,19] It is anticipated that programming a single sequence of ATP will reduce the use of shock therapy in this patient population, and thereby improve the patients' quality of life.

##### ○ maximum output for all VF therapy sequences and FVT sequence 2–6

An initial high output shock may improve first shock success and thus reduce the likelihood of multiple shock episodes. In addition, the slightly longer charge time may allow more non-sustained VT/VF episodes to terminate before the first shock.

#### 2) Strategies to reduce shocks for SVTs

##### ○ tachycardia detection at 330 ms

A treated cut-off of 320 ms has been used in several large primary prevention patient populations. [7,14,20] In the latter two studies, investigators recommended a treatment cut-off between 330 and 350 ms. Detection of only tachyarrhythmias faster than 330 ms should reduce the inappropriate detection of SVTs.

##### ○ VT monitor zone for slow VTs

One recent study showed that only about 5% of patients with primary prevention indications experience monomorphic VT episodes slower than 360 ms. [21] Setting a VT monitor zone between 360 and 330 ms is designed to reduce the inappropriate detection of SVTs, but still allow for identification of VT episodes below the therapy zone.

##### ○ longer detection duration

VF initial beats to detect is set to 30 of 40 beats which may reduce detection of fast but nonsustained SVTs.

##### ○ PR logic (dual chamber) or Wavelet (single chamber)

SVT discriminators reduce detection of sustained SVTs of 300 ms (SVT Limit) or slower.

### Statistical analysis

The primary endpoint is the difference in Morbidity Index incidence density between the study patients programmed to the PREPARE settings and the control population programmed to physician-tailored programming. The PREPARE programming strategy will be considered superior to the physician-tailored programming approach if a statistically significant reduction in the incidence density is demonstrated in the PREPARE group when compared to the historical control.

There were 347 shocked spontaneous VT/VF episodes, 4 events of arrhythmogenic syncope, and no episodes of untreated symptomatic sustained VT/VF in the 691 control population patients followed for 503 years (ID = 0.70). Assuming that the PREPARE programming strategy results in a 25% reduction in the number of shocked spontaneous VT/VF episodes, the rates of arrhythmogenic syncope and untreated symptomatic sustained VT/VF events remain the same, and the same number of years of follow-up, a total of 700 patients will provide at least 95% power for the primary hypothesis, tested at the two-sided significance level of 0.05. Both the Morbidity Index ID and the secondary analysis of the Morbidity Tachycardia Index ID will be tested using the comparison of incidence rates test. [22]

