#### Data collection

These data are collected at the 6 and 12 month scheduled visits and at unscheduled visits: cardiovascular adverse events, cardiovascular medications, VT/VF and SVT episodes, and patient diary.

Adverse events of syncope, near-syncope, and dizziness are collected between visits in a patient diary and evaluated for arrhythmogenic syncope, i.e. syncope or near syncope caused by a VT/VF or SVT episode, and symptomatic VT/VF events i.e. VT/VF events that result in the symptoms of near syncope or dizziness. All events in the PREPARE, EMPIRIC and MIRACLE ICD Trials will be adjudicated by the PREPARE Adverse Event Advisory Committee (AEAC) to identify arrhythmogenic syncope, near-syncope, and dizziness. The review includes the details surrounding each adverse event and the available EGM data for episodes occurring within 24 hours of the event. For the historical controls, where these adverse events were not as rigorously collected, the event will be adjudicated when the record indicated syncope, near-syncope, or dizziness in the narrative of an adverse event.

The differences in data collection methods between studies are always of concern when utilizing a historical control. There are two particular sources of bias when comparing the primary and key secondary endpoints in the PREPARE study to the historical control data: 1) adverse event collection and 2) incomplete adjudication of VT/VF episodes.

Patients in the PREPARE study are required to record adverse events of syncope, near-syncope, and dizziness in a patient diary, in an effort to increase the probability of collecting all occurrences of these events. By contrast, the MIRACLE ICD study relied on patient recall at study visits, and only system and procedure-related adverse events were collected in the EMPIRIC study. These methods of collection in the historical control group likely led to underreporting of syncope related events, and therefore decreased the probability of arrhythmogenic syncopal or symptomatic VT/VF event discovery during these studies. The expected consequence of this data limitation is that higher rates of arrhythmogenic syncope and symptomatic VT/VF events will be recorded in the PREPARE study.

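### The power statement holds syncope and untreated VT/VF rates at the control level, although the data-collection section expects higher recorded rates in PREPARE

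*Protocol article*

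**What the plan says.** All references are to the Protocol article.

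- **Statistical analysis, control data:** "There were 347 shocked spontaneous VT/VF episodes, 4 events of arrhythmogenic syncope", and no untreated symptomatic sustained VT/VF, among 691 control patients followed for 503 years. The incidence density is given as 0.70.
- **Statistical analysis, planning assumptions:** a "25% reduction in the number of shocked spontaneous VT/VF episodes"; that "the rates of arrhythmogenic syncope and untreated symptomatic sustained VT/VF events remain the same"; and "the same number of years of follow-up".
- **Statistical analysis, claim:** "a total of 700 patients will provide at least 95% power for the primary hypothesis", "tested at the two-sided significance level of 0.05".
- **Data collection:** PREPARE patients must keep a diary of syncope, near-syncope and dizziness. MIRACLE ICD relied on what patients recalled at visits. EMPIRIC collected only adverse events related to the system or procedure. The section concludes that control events were probably under-reported, and expects that "higher rates of arrhythmogenic syncope and symptomatic VT/VF events will be recorded in the PREPARE study".
- **Morbidity index and Incidence Density:** arrhythmogenic syncope and untreated sustained symptomatic VT/VF are index components. The primary endpoint counts all index events per year of follow-up.

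**The concern.** The test compares recorded events, so power depends on recorded rates. The Statistical analysis section enters the non-shock components at the control rate, while the Data collection section expects them to be recorded more often in PREPARE. The index is a simple sum, so each extra recorded syncope or untreated event cancels one prevented shock episode, even if the programming cuts shocks exactly as assumed.

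The stated power therefore describes a comparison more favourable than the one the article expects to make. If the result falls just short of significance, a reader relying on 95% power would lean towards concluding that the programming failed, when fuller event capture in PREPARE could have contributed.

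**Working it through.** **Inputs (Statistical analysis section).** Control: 347 + 4 + 0 = 351 events in T0 = 503 years. Shock reduction 25%. Two-sided 0.05, so z = 1.96. PREPARE follow-up T1 is 503 years as the power statement has it. The Design section gives about 700 patients followed for 12 months, so 700 years is used as an upper bound.

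**Assumption (not in the article).** The combined PREPARE count of syncope and untreated VT/VF is k per 503 years, where k = 4m and m is the ratio to control. The ratio applies to the combined count, because the control count of untreated events is zero.

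**Formula.** Two Poisson rates, normal approximation:

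- r0 = 351/503 = 0.6978
- r1 = (0.75 × 347 + k)/503 = (260.25 + k)/503
- power = Φ[(r0 − r1)/√(r0/T0 + r1/T1) − 1.96]

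**Step 1: the plan's own case (m = 1, T1 = 503).** r1 = 264.25/503 = 0.5253. The difference is 0.1725, the standard error √(0.6978/503 + 0.5253/503) = 0.0493, and the ratio 3.50. Power = Φ(3.50 − 1.96) = 93.8%. With T1 = 700 it is 96.2% (96.5% using a pooled variance under the null). The stated figure is thus reproduced to within about one point.

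**Step 2: an excess, with the shock reduction kept.**

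| Ratio m | Events k per 503 years | PREPARE index events per 503 years | Index reduction | Power, T1 = 503 | Power, T1 = 700 (unpooled to pooled) |
|---|---|---|---|---|---|
| 1 | 4 | 264.25 | 24.7% | 93.8% | 96.2–96.5% |
| 2 | 8 | 268.25 | 23.6% | 91.4% | 94.4–94.9% |
| 3 | 12 | 272.25 | 22.4% | 88.4% | 92.1–92.6% |
| 5 | 20 | 280.25 | 20.2% | 80.4% | 85.3–86.1% |

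Example at m = 5, T1 = 503: r1 = 280.25/503 = 0.5572; the difference is 0.1407, the standard error 0.0499 and the ratio 2.82; Φ(2.82 − 1.96) = 80.4%.

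**Step 3: what belongs to this point.** At 503 years the loss due to the excess is 93.8 − 91.4 = 2.4 points for a doubling and 93.8 − 80.4 = 13.4 points for a five-fold excess. At 700 years (unpooled) it is 96.2 − 94.4 = 1.8 and 96.2 − 85.3 = 10.9 points.

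**The case against.** **The effect is small.** The non-shock components are 4 of 351 control events (1.1%), and over a 2- to 5-fold excess power stays at 80% or above. This stands. It limits the weight of the point, but at a doubling or more power is still below the stated figure, if only slightly at 700 years.

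**The assumption may concern programming, not recording.** The sentence can be read as saying that the settings leave the true non-shock rates unchanged, while the Data collection section speaks of what will be recorded. That is a fair reading, and a reader who infers that the article rules out equal rates goes too far: it gives an expected direction and no size. But the test uses recorded counts, so the power figure still needs the recorded rates.

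**The expectation maps only partly onto the index.** The Data collection section refers to symptomatic VT/VF events; the index counts untreated sustained ones. Events in all three trials are also adjudicated, so diary entries need not become index events one for one. This stands for the VT/VF component. The syncope component matches directly.

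**The bias is disclosed and conservative.** Correct: it works against PREPARE. A reader might infer that the asymmetry threatens a positive result, but over-recording in PREPARE cannot produce a false benefit. Disclosure in one section does not, however, carry the bias into the power figure in another.

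**More alarming figures.** A reader might infer that power could collapse; at 503 years a ten-fold excess would give 51%. Nothing in the article supports a ratio of that size.

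**Conclusion.** The point holds as an inconsistency between assumptions. The single figure of at least 95% rests on equal recorded non-shock rates, which the article itself expects not to see. Assuming a 2- to 5-fold excess, power is about 91% to 80% with 503 PREPARE years and about 95% to 85% with 700.

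These figures rest on the assumed ratio, the full 25% shock reduction, and a model of independent Poisson events. A small excess matters little. The range cannot be narrowed from the article, because the base of 4 and 0 events comes from sources that it calls under-reported.

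Two further inferences are not supported. The gap between 93.8% and 95% at equal rates with 503 years is not caused by the recording difference and is a separate matter. The lack of a stated plan to report shock components separately is not a defect either, since an article may leave that to the analysis plan.

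**What to change.** In the Statistical analysis section, replace the equal-rate assumption with one that agrees with the Data collection section: for example, combined syncope and untreated VT/VF events recorded in PREPARE at 2 to 5 times the control count, labelled as an assumption. Give power as the resulting range, with the PREPARE follow-up years used, in place of the single figure.

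The cost is one recalculated sentence and a less favourable stated power. The sample size, endpoint and test do not change.

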### Design

The PREPARE study is a prospective, single arm, multi-center cohort study designed to evaluate the efficacy of a pre-specified strategic profile of VT and VF detection and therapy settings designed for ICD indicated patients with no history of spontaneous sustained symptomatic VT or VF. All study patients received a Medtronic Marquis family ICD system with or without capacity for cardiac resynchronization implanted between October 2003 and April 2005. Approximately 700 patients were enrolled in the United States and the Netherlands and were programmed to the PREPARE parameters and followed for endpoints for 12 months after PREPARE programming.

For the purposes of this study, primary prevention patients are defined as those patients indicated for ICD or CRT + ICD implantation without a baseline history of ventricular fibrillation, ventricular flutter, monomorphic VT, polymorphic VT, or Torsades de Pointes. Patients may have a history of cardiovascular syncope, since the PREPARE findings are intended to be generalized to the primary prevention patient population seen in clinical practice.

• Inclusion criteria required:

○ Initial implantation for primary prevention ICD indications or

○ Prior ICD implantation within 6 months without subsequent

spontaneous VT/VF episodes

• Patients were excluded for:

○ History of spontaneous sustained symptomatic ventricular arrhythmias,

○ An electrophysiology test in the past, with sustained inducible VT < 180 bpm,

○ Any ICD implanted greater than 6 months prior to the study,

○ An ICD implanted within the previous 6 months, with subsequent history of a spontaneous episode of VT or VF appropriately treated with either ATP or shock.

○ Heart transplant

○ Mechanical right heart valve.

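### The stated power of at least 95% is about what independent episodes would give, and the power paragraph shows no allowance for repeat episodes in the same patient

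*Protocol article*

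**What the plan says.** All from the protocol article.

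- **Planning data (Statistical analysis).** "There were 347 shocked spontaneous VT/VF episodes, 4 events of arrhythmogenic syncope, and no episodes of untreated symptomatic sustained VT/VF" among 691 controls with 503 years of follow-up, an incidence density of 0.70.
- **Assumptions (Statistical analysis).** Shocked episodes are taken to fall by a quarter under PREPARE programming, while syncope and untreated events are taken to be unaffected. For PREPARE person-time the paragraph assumes "the same number of years of follow-up" as in the controls.
- **Claim (Statistical analysis).** "a total of 700 patients will provide at least 95% power for the primary hypothesis, tested at the two-sided significance level of 0.05". The test named is a comparison of incidence rates.
- **Endpoint (Incidence Density).** All Morbidity Index events are summed and divided by all years of follow-up, so each repeat episode in a patient counts.
- **Follow-up (Design).** About 700 patients are "followed for endpoints for 12 months after PREPARE programming".

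**The concern.** A plain comparison of two incidence rates takes the variance of each event total to equal its mean. That holds if episodes are independent and patients share a common rate. Shocked episodes in ICD patients need not behave that way: some patients have none and others have several, and the Background section itself refers to patients who receive multiple shocks. The variance of the total then exceeds the mean.

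The stated power is close to the value that independent episodes give, and the paragraph mentions neither between-patient variance nor a clustering allowance. Two things are at stake. If the final test allows for clustering, true power is below the quoted figure, and a non-significant result would be read as stronger evidence than it is. If the final test does not, the two-sided 0.05 level is not held. Under material clustering, the quoted power and the quoted significance level cannot both be right on the stated inputs.

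**Working it through.** **Inputs** (Statistical analysis unless noted)

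- Control: 347 + 4 + 0 = 351 events in 503 years; rate 351/503 = 0.698, which agrees with the stated 0.70.
- PREPARE: 0.75 × 347 + 4 = 264.25 events per 503 years; rate 0.525; rate ratio 0.753.
- PREPARE years T: 503 as written, or up to 700 if about 700 patients each complete 12 months (Design).
- Two-sided 0.05, critical value 1.960.
- Variance inflation f (variance of the event total divided by its Poisson value): not given in the article. Values of 1.5, 2 and 3 are assumed here, equal in both groups.

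**Step 1: the plan's figure, independent episodes (f = 1)**

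Power = Φ(d/SE − 1.960), with d = 0.6978 − 0.5253 = 0.1725 and SE = √(0.6978/503 + 0.5253/T).

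- T = 503: SE = 0.0493, z = 3.497, power = Φ(1.537) = 93.8%. Log-rate, square-root and continuity-corrected versions give 93.4% to 93.9%.
- T = 700: SE = 0.0462, z = 3.730, power = Φ(1.770) = 96.2%.
- 95% is reached at about 583 PREPARE years, with control held at 503.

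The stated figure therefore lies between the two readings of follow-up, under independence.

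**Step 2: clustering, with a test that allows for it**

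Power = Φ(z/√f − 1.960).

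| Assumed f | 503 years | 700 years |
|---|---|---|
| 1 | 93.8% | 96.2% |
| 1.5 | Φ(2.856 − 1.960) = 81% | Φ(3.046 − 1.960) = 86% |
| 2 | Φ(2.473 − 1.960) = 70% | Φ(2.638 − 1.960) = 75% |
| 3 | Φ(2.019 − 1.960) = 52% | Φ(2.154 − 1.960) = 58% |

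At 700 years the inflation that brings power down to 95% is (3.730/(1.960 + 1.645))² = 1.07. The margin above 95% is thus very thin.

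**Step 3: clustering, with the test left unadjusted**

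Two-sided type I error = 2 × (1 − Φ(1.960/√f)): 11% at f = 1.5, 17% at 2, 26% at 3.

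**Step 4: control count treated as already observed**

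With 351 control events fixed and 503 PREPARE years, the test rejects at 300 or fewer PREPARE events, and a Poisson count with mean 264.25 does so with probability 98.6%. With clustering, the normal approximation gives about 90%, 77% and 53% at f = 1.5, 2 and 3. With 700 PREPARE years as well, it gives about 96% at f = 1.5 and 86% at f = 2.

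**The case against.** **The stated figure is not an arithmetic error.** A reader might infer from 93.8% that the claim of at least 95% is miscalculated. The documents do not support that. The gap is 1.2 points, and two readings compatible with the article exceed 95%: 12 months of follow-up in about 700 patients (96.2%), and conditioning on control events already in hand (98.6%). Planning on 503 years when up to 700 are expected is also a conservative assumption rather than a contradiction. This stands in full. For the same reason 93.8% cannot be presented as the highest power the design could have.

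**The inputs are not exact enough for a one-point dispute.** The Morbidity Index has four components, including inappropriate shocks, while the planning paragraph lists counts for three. Whether inappropriate shocks are in the planning count is unclear. This also stands.

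**Silence is not proof that clustering was ignored.** The article is condensed, the analysis plan is not shown, and the reference for the rate test cannot be read here. Nor does the closeness of 95% to the independent-events value prove how the figure was obtained: Step 4 shows that fixed controls, 700 years and an inflation of 1.5 would also give about 96%. But no such combination is stated. The power figure is printed with its inputs, and those inputs contain no variance beyond the event totals.

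**The size is unknown.** The inflation values are assumptions. This stands, and it limits the point to a range. It does not remove it, because at 700 years an inflation of 1.07 already uses up the margin in the two-sample calculation.

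**Conclusion.** The point holds in this form: the stated power is near what independent Poisson episodes give (about 94% at 503 PREPARE years, about 96% at 700), no allowance for repeat episodes within patients is stated, and the endpoint counts every episode. For assumed inflation of 1.5 to 3, power falls to between 81% and 52% at 503 years, or between 86% and 58% at 700 years. Without adjustment, type I error rises to between 11% and 26%. Even on the most favourable combination (fixed controls and 700 years), power is about 86% at an inflation of 2.

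These figures assume equal inflation in both groups, the planned 25% reduction in shocked episodes, and normal approximations. The true inflation cannot be obtained from the article. The difference between 93.8% and 95% is a rounding-level remark only.

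**What to change.** In the Statistical analysis section:

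1. State the PREPARE follow-up years used in the power calculation, and whether the control count is treated as random or as already observed.
2. Quote the independent-events figure that matches: about 94% at 503 years, or about 96% at 700, if both counts are random.
3. Beside it, give power with the between-patient variance of the 691 controls' event counts. With y events and t years per patient and pooled rate r, the inflation factor can be estimated as Σ(y − r·t)² / Σy.
4. Specify the same clustering-robust variance, computed by patient, for the rate comparison itself, for both the primary and the key secondary index.

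The cost is one recalculation from the patient-level control data behind the published totals, and a few sentences. Enrolment, follow-up and treatment are unaffected. The quoted power will probably become less favourable and the confidence interval for the rate difference wider.

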## Background

Implantable defibrillator therapy terminates ventricular tachyarrhythmias and improves survival of patients in multiple populations at risk of sudden cardiac death. [1-3] Initially, ICD therapy was applied only to secondary prevention patients: that is, those who had been resuscitated from a cardiac arrest or other sustained ventricular tachyarrhythmias. The impact of other studies, such as MADIT, MUSTT, MADIT II and SCD-HeFT, as well as the CMS national coverage decision in January of 2005, is that the large majority of patients currently receiving ICDs have primary prevention indications and no symptomatic arrhythmias prior to ICD implantation. [4-8]

There are substantial differences in the clinical and rhythm characteristics of patients with primary and secondary prevention indications for ICD therapy. However, it is an important goal to minimize the morbidity of the therapy for all ICD patients. Patients who receive multiple shocks have difficulty adjusting to the ICD implantation, due to increased anxiety and depression. [9,10] In addition, patients who have not had a significant life-threatening arrhythmic experience such as sudden cardiac death may be less accepting of unnecessary shock therapies.

The EMPIRIC and Painfree Rx studies have shown that a standardized set of VT/VF parameters extensively utilizing SVT discriminators and anti-tachycardia pacing (ATP) therapies can be effective in reducing patient shocks after ICD implantation for a mixed population of primary and secondary prevention patients. [11,12] It is the purpose of the PREPARE trial to evaluate strategies specifically designed to reduce shocks in a population of patients with primary prevention ICD indications with and without cardiac resynchronization indications and therapy.

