#### Incidence Density (ID)

The Morbidity Index incidence density is calculated by dividing the total number of Morbidity Index events by the total number of years of follow-up. The primary endpoint is the difference in Morbidity Index incidence density between the study patients programmed to the PREPARE settings and the control population programmed to physician-tailored programming.

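### The incidence-rate test and the 95% power make no allowance for repeat episodes in one patient or for rates that differ between patients; if events are overdispersed, p-values are too small and power is overstated

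*Protocol article*

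**What the plan says.** The Incidence Density (ID) section defines the primary measure as a pooled ratio, "calculated by dividing the total number of Morbidity Index events by the total number of years of follow-up". Every episode counts, including the second and later ones in the same patient. The primary endpoint is the difference in this ratio between the PREPARE patients and the historical controls.

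The Statistical analysis section assigns one test to the Morbidity Index ID and to the key secondary index; the second half of that sentence reads "the secondary analysis of the Morbidity Tachycardia Index ID will be tested using the comparison of incidence rates test". A significant reduction on the primary comparison is the criterion for superiority, "tested at the two-sided significance level of 0.05".

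The power statement rests on event totals and follow-up years alone. For the controls: "There were 347 shocked spontaneous VT/VF episodes, 4 events of arrhythmogenic syncope, and no episodes of untreated symptomatic sustained VT/VF", in 691 patients over 503 years. The effect is set by "Assuming that the PREPARE programming strategy results in a 25% reduction in the number of shocked spontaneous VT/VF episodes", with the other components and the follow-up unchanged. The result is that "a total of 700 patients will provide at least 95% power for the primary hypothesis".

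The article nowhere mentions correlation within patients, overdispersion, a robust variance or a patient-level model.

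**The concern.** A plain comparison of two person-time rates takes the number of events as its own variance. For patients sampled from a wider population, this holds only if they share one rate and each patient's episodes occur independently. If some patients are more prone to episodes, or one episode makes another more likely, the variance of the total exceeds the count.

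Unequal rates are likely here. The Control population section pools two trials with clearly different patients: mean ejection fraction 21% in MIRACLE ICD against 30.3% in EMPIRIC, and NYHA class III in 57.1% against 13%. That section also warns that a difference in disease severity could skew the results, which presumes that event frequency depends on severity.

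At stake are the type I error of the superiority claim and the meaning of the power figure. This is not a detail left to an unseen SAP, because the article itself fixes the endpoint, the test and the basis of the power.

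**Working it through.** **Inputs (Statistical analysis section).** Control events 347 + 4 + 0 = 351. PREPARE events under the planned effect 0.75 × 347 + 4 = 264.25. Follow-up 503 years in each group. Patients 691 and 700. Two-sided α = 0.05. The variance/mean ratio φ is not given and is an assumption throughout.

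**Step 1: reproduce the plan's figure.** The rates are 351/503 = 0.698 and 264.25/503 = 0.525, a ratio of 0.753. With variance equal to the count and equal follow-up:

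z = (351 − 264.25)/√(351 + 264.25) = 86.75/24.80 = 3.50

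power = Φ(3.50 − 1.96) = 93.8%

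Other standard two-group forms (log rate ratio, square root, exact conditional) give 93.3% to 93.9%. This is close to the stated 95%, and any φ above 1 moves the result further below it.

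**Step 2: allow for overdispersion.** If the true variance is φ times the count:

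- type I error of the planned test = 2 × [1 − Φ(1.96/√φ)]
- power of a test with the correct variance = Φ(3.50/√φ − 1.96)

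A gamma-Poisson simulation serves as a check (691 and 700 patients, 503 years each, φ set in the control group). In it, a patient-level robust test kept its type I error at about 0.05 for every φ.

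| φ (assumed) | Type I error, planned test (formula) | Same, simulated | Valid power (formula) | Valid power, simulated |
|---|---|---|---|---|
| 1 | 0.05 | 0.05 | 94% | 94% |
| 1.25 | 0.08 | 0.08 | 88% | 89% |
| 1.5 | 0.11 | 0.11 | 81% | 83% |
| 2 | 0.17 | 0.16–0.17 | 70% | 73% |
| 3 | 0.26 | 0.26 | 52% | 55–57% |
| 6 | 0.42 | 0.42–0.43 | 30% | about 31% |

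Simulated power is a little higher than the formula because, in the gamma-Poisson model, φ falls with the lower event rate in the PREPARE group.

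**Step 3: thresholds.** Valid power falls to 80% at φ = [3.50/(1.96 + 0.84)]² ≈ 1.56. A result exactly equal to the planned effect stops being significant above φ = (3.50/1.96)² ≈ 3.2.

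**Step 4: what φ could be.** The controls had 347/691 = 0.502 shocked episodes per patient. One common Poisson rate would put 1 − exp(−0.502) = 39% of patients at one or more. If instead a share p of patients holds all episodes, φ is at least 0.502 × (1/p − 1). For assumed shares of 20%, 15% and 10% this gives 2.0, 2.8 and 4.5. The article does not report the actual share.

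**The case against.** **The variance is inferred.** The article names neither Poisson nor a variance formula, and the reference cited for the test is not available. The power calculation supports the usual reading without proving it. Treating the control rate as a fixed constant would give 99.9%, and about 95% even at φ = 1.87, so that route would leave room for overdispersion. But the article describes a comparison of two groups, and a fixed control rate would ignore the sampling error of the controls. The inference stands, labelled as such.

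**Clustering is not shown.** This objection also stands. There are no per-patient counts and no proportion of patients with an episode. A reader might take the Background remark, "Patients who receive multiple shocks have difficulty adjusting to the ICD implantation", as evidence of recurrent episodes. It concerns shocks and psychological adjustment, whereas the index counts episodes that end in a shock, and one episode can contain several shocks.

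**Pooling the two control trials adds little by itself.** Suppose one source (415/691 = 0.60 of patients) had twice the rate of the other (0.40), with 351/691 = 0.508 events per patient overall. The lower mean is 0.508/1.6 = 0.3175, the between-source variance 0.60 × 0.40 × 0.3175² = 0.024, and φ about 1 + 0.024/0.508 = 1.05. The pooling is a sign that rates vary between patients. Larger values of φ need variation within each source, or recurrence within patients.

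**The event base may be incomplete.** The power paragraph describes the 347 as shocked spontaneous VT/VF episodes, while the Morbidity index section also lists inappropriate shocks. If those are not included, the mean and the power are not those of the defined endpoint. The direction of the concern is unaffected.

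**Conclusion.** The point holds in conditional form. On its usual reading, the named test, and the power built on the same totals, make no allowance for repeat episodes or for unequal rates. If events are overdispersed, the direction is certain: p-values too small and power overstated. The size depends on an unreported φ. Across assumed values from 1.25 to 6, type I error runs from about 0.08 to 0.42 and valid power from about 88% to 30%.

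A reader might go further and infer that the primary p-value is certain to be badly wrong, or that the true power is near 30%. The article does not support this. The upper end comes from an assumed φ of 6, and a φ near 1 cannot be excluded. Nor can one say that the plan's confidence intervals are too narrow, since it states no interval method; the point covers only intervals built on the same variance.

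It should still be corrected before analysis. Even φ = 1.5 roughly doubles the nominal error rate of the test that decides superiority.

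**What to change.** Keep the endpoint as total events over total years. Base the primary test, the key secondary test and any confidence interval on a patient-level variance. Suitable choices are a Poisson/GEE model with patient-robust variance and log follow-up as offset, or a patient-level bootstrap of the ID difference. A negative binomial model with the same offset is an alternative. A sensitivity analysis that caps episodes per patient is optional.

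Estimate the dispersion from the per-patient counts of the 691 controls already in hand, state it, and recompute the power from it.

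The cost is a change of wording, slightly more analysis work and probably a less favourable stated power. No new data are needed. If dispersion proves negligible, almost nothing is lost: at φ = 1 the robust test had the same simulated power, about 94%, as the planned one.
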